### Specific Aim 2– To evaluate the kinematic and kinetic differences of non-articulating ESR, articulating ESR, and active plantar flexion ESR feet in individuals with transtibial amputation

Hypothesis 2.1 Plantarflexion forces (i.e. ground reaction forces) at push off /terminal stance will be most symmetrical to the intact limb for active plantarflexion devices, followed by non-articulating ESR feet, and lastly articulating ESR devices.

Hypothesis 2.2 Biomechanical symmetry in gait while negotiating a decline will be greater for both active plantarflexion ESR and articulating ankle ESR conditions compared to non-articulating ESR feet.

Hypothesis 2.3 Biomechanical symmetry in gait while negotiating an incline will be greatest for devices with active plantarflexion, followed by articulating devices, and lastly non-articulating ESR feet.

Hypothesis 2.4 Ambulation at a faster than self-selected walking speed will yield decreased symmetry in articulating ankle ESR and non-articulating ESR feet but not with the active plantar flexion ESR feet.

Hypothesis 2.5 Articulating ESR feet will not yield significant differences in gait symmetry regardless of specific foot assigned within the articulating ESR category.

**Specific Aim 3 – To correlate biomechanical findings with functional and subjective outcome measures and with user preference determined through activity monitoring and user satisfaction to develop guidelines for appropriate prosthetic prescription.**

Hypothesis 3.1 Individuals that commonly negotiate ramps, hills, inclines or declines will show preference for an articulating ankle ESR and/or active plantarflexion ESR feet over non-articulating ESR feet

Hypothesis 3.2 Individuals that have higher step counts, but do so at a low activity level will prefer the active plantarflexion ESR ankle-foot prosthesis.

Hypothesis 3.3 The majority of subjects will chose to utilize a single prosthesis for all activities, and not use different prostheses for different activities, as measured through step activity monitoring and daily activity logs.

Hypothesis 3.4 Step activity performance will, and age will not, correlate with prosthetic feet category that best optimizes function.

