### **Foot Selection:**

Prosthetic ankle-foot units included in this study will be grouped in to three categories: 1) Non-articulating ESR - this group will be any qualifying ESR ankle-foot unit that is commercially available. This will typically be the foot the subject is currently using. This group contains over 100 commercially available prosthetic feet, and will be randomly chosen from all available options that fit the subject’s anatomy if the user does not current have a non-articulating ESR foot. 2) Articulating ESR – this group includes all commercially available options

that have an articulating ankle and also have ESR qualities, currently Endolite Echelon, Fillauer Motion Foot, Freedom Innovations Kinterra, Endolite Elan, Ossur Propriofoot, Hosmer Raize, Otto Bock Triton Smart Ankle, and Ossur Proflex (Figure 2) meet this criteria. 3) Active (Powered) Plantarflexion - the third group will contain all commercially available ESR ankle-foot units with active plantarflexion. Currently, the iWalk BiOM is the only foot that would be classified into the Active Plantarflexion ESR group. If new prosthetic feet-ankle units become commercially available during the course of this study, they will be added to the appropriate groups.

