*Articulating ESR Group:* The articulating ESR group contains mechanical and microprocessor controlled prosthetic ankle-foot units. While there is research comparing these devices to SACH feet and non-articulating ESR feet, there is no current research suggesting any differences between the feet within this group in their effect on functional performance. These prosthetic ankle-foot units have articulation ranges from 9 to 50 degrees within this group, and it has been reported that average range of motion in a healthy individual with an intact lower limb is 20-40 degrees for ankle plantar/dorsiflexion (25). There is no published research to-date as to the ideal range of motion for an individual with transtibial limb loss, so all ankle-foot units will be included. Internal analysis within all groups will be conducted at the completion of this study to substantiate or rebut these groupings, and to determine if there are in fact outliers that should be classified differently clinically or in future research.

*Active Plantarflexion ESR Group:* Criteria for this group includes the following

- Commercially available
- Must be articulating
- Provides plantarflexion energy during terminal stance at a rate that is greater than the total energy absorbed (i.e. >100%)

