### **Specific Aim 1:** Assessment of function using ESR, Articulating ESR and Active Plantarflexion ESR ankle-foot prostheses

Parts 2-4 of the study will address Specific Aim 1. Part 2 will begin with issuing the first of the 3 well-fitting prostheses according to the randomization schedule, including a 1 week acclimation period. At the conclusion of this acclimation period, a battery of outcome measures and surveys (outlined below) will be collected. For Part 3, the subject will receive the second prosthesis according to the established randomization schedule and the initial prosthesis will be returned to the study prosthetist. The subject will again have a one week acclimation period followed by the collection of the same battery of outcome measures and surveys. The third prosthesis will be issued during part 4, and the second prosthesis will be returned to the study prosthetist. The subject will receive the same one week acclimation followed by the battery of outcome measures and surveys.

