The PEQ contains a VAS for pain within the evaluation. Spearman correlations, a statistical measure of the strength of a monotonic relationship between paired data will be calculated to correlate data between pain and functional outcome values across the 3 groups. Linear mixed-effects models will be used to identify statistically significant differences in pain scores and functional outcome variables. In the case of significance, pair-wise comparisons will be tested for significance using linear contrasts with Tukey's Honestly Significant Difference or applying Bonferroni's correction. Finally, stepwise multiple regression will be performed with VAS pain as the dependent variable. The independent variables will be comprised of functional parameters and condition (foot type). Significance will be set at  $p < 0.05$ . Variables will be eliminated if  $p$  is  $> 0.1$ .

*Hypothesis 1.4 There will be no significant differences in functional outcome measures within all tested non-articulating ESR feet regardless of specific foot assigned.*

*Hypothesis 1.5 There will be no significant differences in functional outcomes within all articulating ESR feet tested regardless of specific foot assigned.*

Functional measures will be analyzed by multilevel (site) repeated measures analysis of variance. Because order of prosthesis will be randomized, there should be no order effect. However, order will be included in the initial analysis to test this assumption. When the ANOVA reveals significant differences ( $p < 0.05$ ), we will apply pairwise comparisons using related pairs t-tests to identify the source of differences ( $p < 0.05$ ).

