#### Power Analysis:

| Site                                                | n   | n for subset |
|-----------------------------------------------------|------------|---------------------|
| VA New York Harbor Healthcare System (NYC)          | 30         | 15                  |
| Walter Reed National Military Medical Center (D.C.) | 30         | 15                  |
| VA Puget Sound Healthcare System (Seattle)          | 30         | 0                   |
| James J. Peters VA Medical Center (Tampa)           | 30         | 0                   |
| TOTAL                                        | 120 | 30           |

Figure 7. Total Subjects per site to be seen over the course of 3 year period

#### Specific Aim 1

Functional measures will be analyzed by multilevel (site) repeated measures analysis of variance. Because order of prosthesis will be randomized, there should be no order effect. However, order will be included in the initial analysis to test this assumption. Assuming an alpha error rate of 5% and within-group standard deviation of 5, 120 subjects will provide over 98% power to detect a 3 unit difference between at least two of the ESR groups for each of the functional measures.

### Specific Aim 2

Kinematic and kinetic measures will be analyzed by multilevel (site) repeated measures analysis of variance. Because order of prosthesis will be randomized, there should be no order effect. However, order will be included in the initial analysis to test this assumption. Assuming an alpha error rate of 5% and within-group standard deviation of 10, 30 subjects will provide 72% power to detect a 6-unit difference between at least two of the ESR groups for each of the measures.

### Specific Aim 3

This analysis will be performed using paired t-test to determine correlations between prosthesis chosen as per SAM data and which functional outcome measures are indicative of that choice. Additionally pair t-test will be performed between kinematic and kinetic data to again correlate with the prosthetic choice of the subject as demonstrated through the SAM data. Finally all SAM data will be evaluated against the activity journal to determine the roll of a specific activity goal and a specific prosthesis.

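### Hypotheses 1.4 and 1.5 are given paired tests that have no pairs, and 1.4, 1.5 and 2.5 count non-significance as support without any margin

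*Protocol*

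**What the plan says.** Three hypotheses predict that feet within one category do not differ. Hypothesis 1.5 reads "There will be no significant differences in functional outcomes within all articulating ESR feet tested regardless of specific foot assigned", and Hypothesis 1.4 is its counterpart for non-articulating feet. Hypothesis 2.5, in the 30-subject gait subset, reads "Articulating ESR feet will not yield significant differences in gait symmetry regardless of specific foot assigned within the articulating ESR category". None of them carries a margin.

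In the section headed SAI: Data and Statistical Analysis, Hypotheses 1.4 and 1.5 share one method: a multilevel (site) repeated-measures ANOVA and, if it is significant, "we will apply pairwise comparisons using related pairs t-tests to identify the source of differences". Hypothesis 2.5 falls under Aim 2. There the SA2 Statistical Analysis section names linear mixed models by foot type with Tukey or Bonferroni contrasts, and the Power Analysis section names repeated-measures ANOVA.

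On the design, Foot Selection defines three categories. It names eight articulating feet and one powered foot, and says of the non-articulating category: "This group contains over 100 commercially available prosthetic feet". Part 1a provides for two additional prostheses besides the subject's own. The Specific Aim 1 section says "Part 2 will begin with issuing the first of the 3 well-fitting prostheses according to the randomization schedule", and the second and third follow in turn.

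The purpose of the within-category work is given under Justification for inclusion of all commercially available feet: "Internal analysis within all groups will be conducted at the completion of this study to substantiate or rebut these groupings".

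The Power Analysis section states, for Aim 1, "Assuming an alpha error rate of 5% and within-group standard deviation of 5", that "120 subjects will provide over 98% power to detect a 3 unit difference between at least two of the ESR groups". For Aim 2 it gives 72% power with 30 subjects for 6 units and an SD of 10. Both statements concern differences between categories.

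**The concern.** With three categories and three prostheses per subject, a comparison of two feet in the same category is always a comparison of different people. A related-pairs t-test has nothing to pair. A within-subject ANOVA answers a different question, whether the categories differ.

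Non-significance is the predicted result, so the smaller and noisier the comparison, the more easily each hypothesis appears confirmed. The Protocol means to use that result to judge its own three-category grouping and to find outlying feet. Its prescription criteria are built on those categories. A reader could take the power stated for the category comparison as assurance for the within-category question, which it does not cover.

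**Working it through.** **Inputs.** Power Analysis: 5% level (sidedness not stated; two-sided assumed); Aim 1 N = 120, SD 5, 3 units; Aim 2 N = 30, SD 10, 6 units. Foot Selection: eight articulating feet. My assumptions: even spread over models, no dropout, and the stated SDs taken as between-subject SDs within a condition.

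**1. The Protocol's own figures (between categories).** Paired t, SD of a difference = SD × √(2(1 − ρ)), noncentrality = d√N / SD of the difference.
- Aim 1, ρ = 0: SD of difference 5√2 = 7.07; noncentrality 3√120 / 7.07 = 4.65; power 99.6%. Repeated-measures ANOVA with equally spaced means and ρ = 0 gives 99.0%. Both agree with the stated figure of over 98%.
- Aim 2, ρ = 0: SD of difference 14.14; noncentrality 6√30 / 14.14 = 2.32; power 61%. The paired t reaches 71% at ρ = 0.20 and 74% at ρ = 0.25. A one-sided test at ρ = 0 gives 73%. The stated 72% is attainable, but needs an unstated correlation or a one-sided test.

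**2. Available pairs.** Three prostheses over three categories, one per category, leave zero same-category pairs within a subject. One per category is inferred: the randomization section does not say it outright, but the comparison of three conditions requires it.

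**3. Hypothesis 1.5, run between subjects.** n = 120 / 8 = 15 per model.
- Pairwise: SE = 5√(2/15) = 1.826; noncentrality 3 / 1.826 = 1.643; 28 df; critical t 2.048; power 35%. The 95% CI half-width is 2.048 × 1.826 = 3.7 units, wider than the 3 units planned for.
- Omnibus: λ = n Σ(μ − mean)² / SD², on 7 and 112 df.

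| Pattern of true means | Σ(μ − mean)² | λ | Power |
|---|---|---|---|
| Two feet 3 units apart, rest midway | 4.5 | 2.7 | 17% |
| One foot differs by 3 | 7.875 | 4.725 | 28% |
| Half the feet shifted by 3 | 18 | 10.8 | 62% |

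**4. Hypothesis 2.5, run between subjects.** n = 30 / 8 = 3.75 per model (fractional n used as an average).
- Pairwise: SE = 10√(2/3.75) = 7.30; noncentrality 6 / 7.30 = 0.82; 5.5 df; critical t 2.50; power 11%. The CI half-width is about 18 units, three times the planned 6.
- Omnibus on 7 and 22 df, same three patterns at 6 units: λ = 0.675, 1.18 and 2.7; power 7%, 8% and 14%.

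**5. Hypothesis 1.4.** The number of non-articulating models actually worn is not given. Over an assumed range, pairwise power for 3 units is 53% with 5 models (24 each), 29% with 10, 16% with 20, 11% with 30 and 7% with 60. Foot Selection says this foot will usually be the subject's own, so differences between models are also mixed with differences between their wearers.

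**The case against.** Several stronger readings are tempting, and the document does not support them.

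- **That the whole analysis cannot be executed.** Only the paired step, and any within-subject effect of foot model, is impossible. A multilevel ANOVA could carry foot model as a between-subject factor; the Protocol does not specify one. Part of the paragraph also recurs as the general Aim 1 method under Power Analysis, so the paired tests may have been meant for the three categories. In that case Hypotheses 1.4 and 1.5 have no test of their own.
- **That paired tests are also prescribed for Hypothesis 2.5.** They are not. Its problem is the missing margin, the small subset, and an Aim 2 model whose factor is foot type, not foot model.
- **That the grouping would nearly always be confirmed.** For Hypothesis 1.5, a real difference is missed in 38% to 83% of trials per outcome, depending on the pattern. Across the five functional outcomes listed under Hypothesis 1.2, if all carried the effect and were independent, at least one omnibus test would be significant in 1 − (1 − 0.28)⁵ = 81% of trials for one differing foot, or 1 − (1 − 0.167)⁵ = 60% for two extremes. Correlation lowers both figures, and with no true difference the same rule gives 1 − 0.95⁵ = 23%. Using the subject's other two conditions as covariates (assumed free of foot effects) would raise pairwise power from 35% to 40%, 49% or 68% at within-subject correlations of 0.3, 0.5 or 0.7. No correlation is stated.
- **That articulating-foot comparisons are confounded by weight, height and activity level.** The randomization section has devices selected at random. Those characteristics may only set the specification of a foot already selected. Confounding is clear only for the non-articulating feet.
- **That the category comparisons fail if feet differ within a category.** They remain valid as comparisons of the commercially available categories. The Protocol also plans to look for outliers and states no rule that non-significance proves sameness.

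What stands: the missing pairs, the no-difference wording without a margin, and power stated only for another comparison.

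**Conclusion.** The point holds. The related-pairs tests cannot be carried out for Hypotheses 1.4 and 1.5, and the repeated-measures ANOVA as described compares categories. For 1.4, 1.5 and 2.5, a non-significant result would be weak evidence that a grouping is sound. With the Protocol's own differences and SDs, the between-subject comparison has modest power for 1.5 and very low power for 2.5. The pairwise intervals are wider than the differences the study was planned to detect. For 1.4 the power cannot be fixed without knowing how many models are worn, and the comparison is confounded in any case. The figures rest on an even spread over eight models, no dropout, a two-sided 5% level and one outcome at a time. Uneven spread or dropout would generally lower them.

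**What to change.** - For Hypotheses 1.4 and 1.5, replace the related-pairs tests with a linear mixed model per outcome over all three conditions: category fixed, subject random, foot model nested in category. Adjust for weight, height and activity level as a precaution.
- For Hypothesis 2.5, add foot model within category to the Aim 2 mixed model.
- Report the between-foot variance component and foot-specific estimates with 95% CIs.
- Reword the three hypotheses so that a non-significant result does not count as support for the grouping. For 1.5, claim similarity only if the interval lies inside a margin stated in advance for that outcome; otherwise report it as inconclusive. One margin cannot serve a walking distance, a time in seconds and ordinal scores.
- Treat 1.4 and 2.5 as descriptive.

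The cost is wording in the Protocol and any analysis plan; no new data are needed. The drawback is that similarity will probably not be shown. With 15 subjects per model, a pairwise 95% interval of ±3.7 units cannot fit inside, for example, a ±3-unit margin. The sponsor gives up a simple no-difference statement for one the data can support.

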### **Randomization of Foot Selection and Order of Evaluation**

After enrollment, the prosthetic devices for each subject, as well as the order in which they will be evaluated, will be randomized using a computer generated algorithm that randomly selects from all available devices and then assigns the order. As determined by subject's weight, height and activity level (activity level rating is based on parameters set by the particular manufacturer/foot), each randomly selected foot will be purchased from the manufacturer by the study coordinator, under the supervision of the principal investigator, at the VANYHHS.

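### For H1.5 (and, with less force, H1.4) the Protocol names a category-level repeated-measures ANOVA with paired follow-up tests, although specific feet are compared between subjects; no product term or use of the subject's other-foot scores is stated

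*Protocol*

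**What the plan says.** In the Protocol section headed SAI: Data and Statistical Analysis, H1.4 and H1.5 share one analysis paragraph: "Functional measures will be analyzed by multilevel (site) repeated measures analysis of variance". Order enters the initial analysis, and a significant ANOVA is followed by related-pairs t-tests. The ANOVA and order wording returns under Power Analysis for the comparison of the three ESR groups, and the same t-test step is given for H1.2, which compares the three conditions.

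Under Foot Selection, eight articulating products are listed ("currently Endolite Echelon, Fillauer Motion Foot, Freedom Innovations Kinterra, Endolite Elan, Ossur Propriofoot, Hosmer Raize, Otto Bock Triton Smart Ankle, and Ossur Proflex"). The powered category holds one: "Currently, the iWalk BiOM is the only foot that would be classified into the Active Plantarflexion ESR group". Products that reach the market later are to be added. The non-articulating foot is typically the subject's own, from more than 100 on the market.

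Each subject is tested on three prostheses, which I read as one per category, with the same battery after each.

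H2.5 makes the parallel claim for gait: "Articulating ESR feet will not yield significant differences in gait symmetry regardless of specific foot assigned within the articulating ESR category". Its analysis text, SA2 Statistical Analysis, is a linear mixed model with foot condition as predictor and a subject-level random term.

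**The concern.** The paragraph for H1.4 and H1.5 is the category analysis carried over to a product question. Categories are compared within subject. Products inside a category are not, because no subject wears two of them. Two things follow.

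- The related-pairs t-test cannot be carried out between two articulating feet.
- Without a product term, the stated ANOVA does not address the hypothesis. Depending on how it is completed, differences in ability between subjects may or may not be removed from the product comparison.

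The stakes are more than technical. The justification for including all commercially available feet says that an internal analysis within groups will confirm or overturn the three categories, and the prescription criteria rest on those categories. An imprecise comparison is likely to find no significant difference whether or not one exists, which is the result that H1.4 and H1.5 predict.

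**Working it through.** **1. The plan's own figure.** Inputs from Power Analysis: "Assuming an alpha error rate of 5% and within-group standard deviation of 5", and "120 subjects will provide over 98% power to detect a 3 unit difference between at least two of the ESR groups". One-way noncentral F with category means −1.5, 0 and +1.5, SD 5 and 120 per condition: λ = 120 × (1.5² + 1.5²)/5² = 21.6 on 2 and 357 df, power 0.990. The figure reproduces, but for categories. No power is stated for products within a category.

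**2. One pair of articulating feet (H1.5).** Assume an equal spread, 120/8 = 15 per foot, and SD 5 between subjects within a condition. Raw SE = 5 × √(2/15) = 1.83. Power for 3 units = Φ(3/1.83 − 1.96) = 0.38, against over 98% for categories.

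**3. Adjusting for the same subject's powered-foot score.** Let ρ be the correlation of one subject's scores on two feet. The Protocol does not give it, so a range is shown. The residual SD becomes 5√(1 − ρ²), which is worth 1/(1 − ρ²) times as many subjects.

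| ρ | Residual SD | SE | Power, 3 units | Equivalent n |
|---|---|---|---|---|
| 0 (raw) | 5.00 | 1.83 | 0.38 | ×1 |
| 0.5 | 4.33 | 1.58 | 0.48 | ×1.33 |
| 0.7 | 3.57 | 1.30 | 0.63 | ×1.96 |
| 0.8 | 3.00 | 1.10 | 0.78 | ×2.78 |
| 0.9 | 2.18 | 0.80 | 0.96 | ×5.26 |

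These are single pairs at an unadjusted two-sided 5%. With Bonferroni over all 28 pairs, power is 0.06 raw and 0.33 at ρ = 0.8.

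**4. Overall test, one foot off by 0.6 SD.** λ = 15 × 0.6² × (1 − 1/8) = 4.725 on 7 and 112 df, power 28%. Dividing λ by 1 − ρ² gives 5.43, 7.38, 13.1 and 24.9 at ρ = 0.36, 0.6, 0.8 and 0.9, and power 32%, 44%, 72% and 96%. Simulation with feet drawn at random (uneven counts, four sites) runs slightly lower: about 27% raw, and 29–31%, 40–44%, 68–71% and 93–94% adjusted. Type I error stays at 4–6% both ways.

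**5. Product as a between-subject main effect.** Averaging over the three conditions shrinks the effect to 0.6/3 = 0.2 SD, with variance (1 + 2ρ)/3. At ρ = 0.8, λ = 15 × 0.2² × 0.875/0.867 = 0.61 and power is about 7%; over the whole range of ρ it is 7–8%.

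**6. All three conditions with a subject effect and a product term.** If the non-articulating score also contributes, the residual variance is 1 − 2ρ²/(1 + ρ). At ρ = 0.8 this is 0.289, so SE = 5 × √(0.289 × 2/15) = 0.98, against 1.10 with the powered score alone. An ANCOVA on both other scores gives the same value.

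**7. H2.5.** 30/8 = 3.75 subjects per foot, SD 10, 6 units. Raw SE = 10 × √(2/3.75) = 7.30, power 0.13. At ρ = 0.9, SE = 3.18 and power 0.47.

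**The case against.** **A reader might infer that the plan discards the powered-foot score.** The text does not say so. Nothing excludes that score, and a repeated-measures model covers all three conditions. With a subject effect and a product term it would use the powered score slightly better than an ANCOVA on that score alone (step 6). What stands is narrower: no product term is stated, other completions of the same sentence are much weaker (steps 4 and 5), and the paired follow-up fits none of them.

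**Model terms are commonly left to the SAP, which is not at hand.** That is fair for a covariate list. It does not cover an analysis that the Protocol does name for these hypotheses and that cannot be carried out as written.

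**The gain depends on an unknown ρ.** This stands. The only hint is Aim 2: "30 subjects will provide 72% power to detect a 6-unit difference between at least two of the ESR groups" needs a correlation of roughly 0.15 to 0.36 to reproduce, where adjustment is worth only 1.02 to 1.15 times n.

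**A reader might also infer that the unadjusted comparison is biased,** because weight, height and activity level appear where the Protocol says "each randomly selected foot will be purchased from the manufacturer by the study coordinator". The same section says that the algorithm selects at random from all available devices, and those factors may govern only the size or stiffness ordered. Any false-positive rate built on a restricted draw would rest on an assumed restriction, so none is claimed here.

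**The powered score is not a baseline.** Many subjects will give it after wearing the articulating foot, and no washout is described beyond one week of acclimation. Adjustment therefore relies on negligible carryover.

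**Conclusion.** The point holds for H1.5. The named analysis is the category analysis, its follow-up test has no pairs to work on, and it states neither a product term nor a role for the subject's other-foot scores. Completed without them, the overall test has about 27% power for one foot off by 0.6 SD, or 7–8% as a between-subject main effect. With the powered score it has about 29–32%, 40–44%, 68–72% and 93–96% at ρ = 0.36, 0.6, 0.8 and 0.9. The gain is therefore small if ρ is low and large if it is high. This assumes 15 subjects per foot on average, no dropout, and negligible carryover.

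It holds with less force for H1.4. Those feet are mostly the subject's own and spread over many products, so adjustment helps precision but cannot supply randomisation or fill sparse cells. H2.5 is not rescued: its model already has a subject-level random term, and about 4 subjects per foot is too few. In no case does a non-significant result show that the feet are alike. The category comparisons of Aim 1 are not affected.

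**What to change.** In the H1.4/H1.5 paragraph of the Aim 1 analysis section:

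- **H1.5:** fit one mixed model to all three conditions, with a random subject effect and fixed effects for category, specific product within category, site and order. Non-articulating products are too many for fixed effects in 120 subjects and are better entered as a random term. Equivalently, use an ANCOVA of the articulating-foot score on product, site and order, with the same subject's powered-foot score, and optionally the third foot's score, as covariate.
- **Follow-up:** replace the related-pairs t-tests with model-based product contrasts, adjusted for multiplicity and reported with confidence intervals.
- **Powered product:** add it as a term if a second one enters the study.
- **SAI and HAI:** use an ordinal method, since the Protocol itself treats them as ordinal under H1.1.
- **H1.4:** label the result descriptive.
- **H2.5:** state that about 4 subjects per foot allows only imprecise estimates, and report intervals.

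The cost is a wording change, a few degrees of freedom, and reliance on negligible carryover into the powered-foot score, which the order term helps to examine. No new data are needed.
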